## Abstract

**Background:**

Hospitalization is a common method to intensify care for patients experiencing a psychiatric crisis. A short-term, specialised, out-patient crisis intervention by a Crisis Resolution Team (CRT) in the Netherlands, called Intensive Home Treatment (IHT), is a viable intervention which may help reduce hospital admission days. However, research on the (cost-)effectiveness of alternatives to hospitalisation such as IHT are scarce. In the study presented in this protocol, IHT will be compared to care-as-usual (CAU) in a randomized controlled trial (RCT). CAU comprises low-intensity outpatient care and hospitalisation if necessary. In this RCT it is hypothesized that IHT will reduce inpatient days by 33% compared to CAU while safety and clinical outcomes will be non-inferior. Secondary hypotheses are that treatment satisfaction of patients and their relatives are expected to be higher in the IHT condition compared to CAU.

**Methods:**

A 2-centre, 2-arm Zelen double consent RCT will be employed. Participants will be recruited in the Amsterdam area, the Netherlands. Clinical assessments will be carried out at baseline and at 6, 26 and 52 weeks post treatment allocation. The primary outcome measure is the number of admission days. Secondary outcomes include psychological well-being, safety and patients’ and their relatives’ treatment satisfaction. Alongside this RCT an economic evaluation will be carried out to assess the cost-effectiveness and cost-utility of IHT compared to CAU.

**Discussion:**

RCTs on the effectiveness of crisis treatment in psychiatry are scarce and including patients in studies performed in acute psychiatric crisis care is a challenge due to the ethical and practical hurdles. The Zelen design may offer a feasible opportunity to carry out such an RCT. If our study finds that IHT is a safe and cost-effective alternative for CAU it may help support a further decrease of in-patient bed days and may foster the widespread implementation of IHT by mental health care organisations internationally.

**Trial registration:**

The trial is registered in the Netherlands Trial Register as # NTR-6151. Registered 23 November 2016.

## Background

For many years hospitalisation has been the indicated care modality for patients experiencing a psychiatric crisis. Alternatives are available [1, 2] such as treatment by outpatient Crisis Resolution Teams (CRTs) [3–6] which are named Intensive Home Treatment (IHT) teams in the Netherlands [7].

There are several arguments from professionals and patient movements to treat people in the community and not in the hospital. Hospital admission can be harmful and stigmatizing to patients while relationships between patients, their relatives and professionals are different and less dominated by inequalities of power when crises are managed in the patients’ own homes.

Social and environmental triggers can contribute to a crisis. By visiting the patient’s home, these triggers can better assessed and addressed. Learning coping skills can be more effective in the environment where these are needed and can help to prevent future crises. Professionals can better respond to the needs of patients and their relatives if they meet them in their own social environment [8, 9]. In addition to these arguments, economic and political pressure encourages community mental health care to develop further. Our working definition of a psychiatric crisis is a situation in which the severity of current acute clinical and social problems and associated risks indicate that admission to an acute psychiatric ward is necessary [10].

Treating patients during a psychiatric crisis may entail intensifying already existing care provided by community mental health teams as in (Functional) Assertive Community Treatment ((F)ACT) teams [11–13]. This care modality is most often prescribed for patients with a disabling Severe Mental Illnesses (SMI), who need intensified care for a long duration of time. But there are also patients experiencing a psychiatric crisis with a need for care of varying intensity. For those patients CRTs can provide an acute intensive specific short-term crisis treatment in their home setting [6]. With such an intervention, patients can stay in their own social environment, while psychiatric and social problems can be assessed and addressed by professionals in cooperation with family or friends of the patient.

### Current evidence base

In a recent Cochrane review on psychiatric crisis interventions [14] eight RCT studies have been included. In five of the eight studies, crisis care was part of the overall care package, while in two studies a telephone answering service comprised the crisis resolution intervention. Treatment of a psychiatric crisis by a specialized CRT team was to our knowledge only investigated in the RCT of Johnson et al. (2005) [15]. Johnson and colleagues compared CRT with CAU, consisting of hospitalisation or a community mental health approach. They found a significant difference in the number of patients hospitalised at 8 weeks (IHT: 36%, CAU: 69%, *p* < 0.0005) and 6 months (CRT: 47%, CAU: 75%, p < 0.0005) after crisis initiation. Eight weeks after crisis initiation, outpatient crisis care improved the mental and social well-being of patients more than CAU, as measured by the Health of the Nation Outcome Scale (HoNOS). However, this effect evaporated 6 months after crisis initiation [15].

Quasi-experimental research, often a comparison between an area with and without CRT, and pre-post CRT care evaluations found reduced hospitalization rates following CRT [5, 16, 17] and fewer days in the hospital [14, 17] when compared to care without a CRT service. Clinical and social outcomes were similar in CRT conditions compared with non-CRT care [18]. Based on pre-post intervention evaluations, Kilian et al. (2016) found that CRT was more effective than admission with respect to HoNOS scores (b = − 4.43; *p* = 0.02) and reductions of depressive symptoms measured by the Hamilton Depression scale (HAMD) (b = − 4.11; *p* = 0.004), but not with regard to the total score of psychotic symptoms measured by the Positive and Negative Syndrome Scale (PANNS) (b = − 4.51; *p* = 0.134). Outpatient crisis care was more acceptable and satisfactory to service users [17, 19], their families and other relatives and reduced the stigmatization inherent to hospitalisation [20] than inpatient care. Burden (such as disruption to daily routine, social life and susceptibility to physical illness) was also reduced for out-patients, their families and other relatives [14, 20].

A recent prospective cohort study performed in Germany included 118 patients with acute mental disorders and found early evidence for the cost-effectiveness of CRT teams compared to hospitalisation [21]. However, methodological limitations, such as different target populations in different studies and variations in study designs complicate the interpretation of the findings [5, 17, 19]. Given the limited evidence base, there is an urgent need for more effectiveness studies on CRT.

## Methods/design

### Research aims and hypotheses

The primary objective of this study is to test whether IHT reduces in the number of inpatient days per patient in the year following psychiatric crisis compared to CAU. Based on previous research [14, 15, 22, 23] and the naturalistic IHT project evaluation in Amsterdam [24] we hypothesize that IHT will lead to a 33% reduction in the number of hospitalisation days at 52 weeks post-randomisation, compared to CAU. This translates to an average reduction of 20 hospitalisation days: 40 days (SD = 40) for IHT and 60 days (SD = 55) for CAU.

### Secondary hypotheses

*Safety.* With regard to safety it is expected that patients in the IHT condition will report the same amount or less symptoms of social malfunctioning and aggression than CAU patients [17].*Psychiatric symptoms*. With regard to psychiatric symptoms it is expected that participants in the IHT condition will report the same amount or less symptoms than CAU patients [15].*Treatment satisfaction.* Higher treatment satisfaction treatment of the participants and their relatives [20, 25] in the IHT is expected compared to CAU.

Alongside this RCT, an economic evaluation will be performed in order to assess the cost-effectiveness and cost-utility of IHT compared to CAU.

### Design

The trial in this protocol is designed as a 2-centre, 2-arm Zelen double consent open label RCT, to test the efficacy and cost-effectiveness of IHT against CAU. This design is chosen after careful consideration and fruitful discussions between the researchers and the IHT professionals and has been approved by the Medical Ethics Committee of VU University Amsterdam (MEtC VUmc) as #NL55432.029.16.

During the first contact with professionals following the start of a psychiatric crisis patients are randomly allocated to one of the two treatment modalities, IHT or CAU. This allocation takes place in a 2 (IHT): 1 (CAU) ratio (for reasons of staff and facility capacity). Consent to participation in the trial and to treatment allocation will be sought as soon as the psychiatric condition of the patients is stabilized, ultimately 3 weeks after intake.

According to the Zelen double consent design all participants will be fully informed about the study during the first meeting with a member of the research group and before consent is sought [26]. This implies that they get information about treatment allocation based on pre-randomisation, study procedures, treatment options, and the possibility to cross-over to the other treatment condition, before they are asked to sign the informed consent form. Only patients who provide written informed consent are included in the study. Participants who cross over between the two conditions will be followed up and analysed as members of the trial arm to which they were originally allocated according to the intention to treat principle [27].

### Study procedure

#### Recruitment

Arkin and GGZ inGeest are the two largest mental health care organisations in Amsterdam, the Netherlands and provide in- and outpatient psychiatric care in Amsterdam for children and adults of all ages. The Psychiatric Emergency Service Amsterdam (PES) is a cooperation between these two organisations. Referrers to PES include general practitioners, other mental health professionals and the police. A professional of PES performs psychiatric assessments, prepares a treatment plan with the patient in cooperation with his family and other professionals, and provides care as described in the treatment plan. PES is available 24 h a day, 7 days a week. The IHT teams are part of PES.

In this study, participants are recruited via IHT teams and the in-patient facilities of Arkin and GGZ inGeest between 8.30 AM and 10.00 PM. During the night, between 10:00 PM and 8:30 AM, PES Amsterdam is functioning as a gatekeeper for Arkin and GGZ inGeest. During night hours patients assessed by this service will receive CAU, i.e. voluntary or involuntary psychiatric admission or community-based care, with support from PES if necessary. The next day, these patients will be screened to check if they meet the in/exclusion criteria for this study. If participants have been admitted to a psychiatric ward during the weekend, they will be screened for study participation the next working day.

#### Participants

All patients are recruited from mental health care organisation Arkin and InGeest in Amsterdam which provide high intensive psychiatric care, IHT treatment or admission to a psychiatric ward. For this study the following in- and exclusion criteria apply:

#### Inclusion criteria

A psychiatrist must state that admission to a clinical crisis care unit is indicated, if necessary on a compulsory basis. This decision is based on clinical outcomes, judgments of other professionals and information from informal caregiversPatient is diagnosed with at least one axis I or II disorderThe patient is a resident of Amsterdam, Diemen or Driemond, the Netherlands.Age between 18 and 65 years oldAbility to read and understand the Dutch languageWritten informed consent has been provided by patient

#### Exclusion criteria

Patient is homelessPrimary diagnosis of the patient is substance use disorder for which referral to a specialized treatment unit is indicatedPatient is currently receiving (F)ACT carePatient has previously received IHT treatment

#### Screening and pre-randomisation

Patients will be screened and pre-randomised by members of the IHT teams or by the patient placement desks of the treatment organisations. For the members of these teams, an online pre-randomisation tool to check whether the in- and exclusion criteria are met has been developed. Patients who do not meet the in- and exclusion criteria will not be included in the study and receive any treatment deemed necessary. Patients who meet the in- and exclusion criteria will be pre-randomised to IHT or CAU.

Pre-randomisation is performed using a seeded pseudo random number generator (Mersenne twister). The seed is based on patient characteristics, to ensure that a given patient is allocated to the same trial arm in case the randomisation procedure would be run more than once. This is necessary because it sometimes happens that in the midst of a psychiatric crisis two or more health care workers may fill out the screening and allocation tool for the same person. The outcome of the pre-randomisation is not only known by the one who is pre-randomising but the outcome is also sent to members of the research team.

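### The arm is recomputed from patient characteristics entered by staff who see the result, so neither one arm per patient nor concealment is assured

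*Protocol article*

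**What the plan says.** All of the following is in the protocol article.

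- **Who runs the tool** (Screening and pre-randomisation): "Patients will be screened and pre-randomised by members of the IHT teams or by the patient placement desks of the treatment organisations". The same online tool checks the criteria and produces the allocation.
- **Order of steps** (same section): "Patients who meet the in- and exclusion criteria will be pre-randomised to IHT or CAU".
- **How the arm is generated** (same section): a seeded Mersenne twister, about which the article says "The seed is based on patient characteristics, to ensure that a given patient is allocated to the same trial arm". The reason given is that, during a crisis, "two or more health care workers may fill out the screening and allocation tool for the same person".
- **Who learns the arm** (same section): the person running the tool sees it, and the researchers are notified as well.
- **The main clinical criterion** (Inclusion criteria): "A psychiatrist must state that admission to a clinical crisis care unit is indicated".
- **After allocation** (Design; Consent and mental competence): a clinician judges competence, consent is then sought, and only consenting patients are included.
- **Blinding and staff preference** (Blinding; Discussion): the trial is open label. The Discussion accepts that professionals may lean towards one condition and answers this with regular meetings with them.

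**The concern.** The seed is meant to give each patient one arm however often the tool is run. It does so by recalculating the arm, not by looking up a stored result, so the protection depends on the seed fields being typed the same way each time. The situation it is meant for, several workers completing the tool for one patient in crisis, is one in which entries are likely to differ.

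The people who enter the data may also deliver one of the treatments, and they see the arm. Eligibility and allocation sit in one tool, and no step is described that fixes the eligibility entries before the arm appears. The project number cannot identify the patient at this point, because it is assigned only after consent (Handling and storage of data and documents).

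At stake is the comparability of the arms on the primary outcome. If the patients whose arm changes differ in expected inpatient days from those whose arm stays, the contrast is biased. Intention-to-treat analysis preserves whatever allocation was recorded, so it cannot correct selection at this step.

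**Working it through.** **Inputs from the protocol article**

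- Allocation 2 (IHT) : 1 (CAU), so P(IHT) = 2/3 and P(CAU) = 1/3 (Design). The planned 153 and 77 agree: 153/230 = 0.665 (Sample size calculation).
- Planned effect 60 − 40 = 20 days (same section).
- The total of 230 can be reproduced. A two-sample comparison with pooled SD √((40² + 55²)/2) = 48.09, two-sided alpha 0.05, power 0.80 and 2:1 allocation gives 207, and the two 5% allowances bring this to 228–230. The point below does not depend on that figure.

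**Step 1: what a repeat run does**

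Identical seed entry: a seeded generator returns the same number, so the arm never changes. A simulation of 100,000 patients with a Mersenne twister gave agreement in 100%.

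Differing seed entry (assumed to act as an independent draw):

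- CAU becomes IHT with probability 2/3 (simulated 0.668).
- IHT becomes CAU with probability 1/3 (simulated 0.336).
- Two workers whose seed entries differ get conflicting arms with probability (2/3)(1/3) + (1/3)(2/3) = 4/9 = 0.44.

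For k altered entries, the chance of having seen the other arm at least once is:

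| k | CAU to IHT: 1 − (1/3)^k | IHT to CAU: 1 − (2/3)^k |
|---|---|---|
| 1 | 0.67 | 0.33 |
| 2 | 0.89 | 0.56 |
| 3 | 0.96 | 0.70 |

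**Step 2: how large a bias could be (assumed inputs)**

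The article gives no rate of repeat entry and no severity difference, so a range is used. Let f be the share of first CAU results re-entered once with altered data. Let D be the number of days by which the moved patients' expected stay is shorter than that of the unmoved CAU patients. The CAU patients as first drawn are taken to be comparable with the IHT patients as first drawn, and the true treatment effect is left out.

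- Share of CAU results that move: r = f × 2/3.
- Share of all patients that move: m = (1/3) × r.
- Shift in the CAU mean: + D × r.
- Shift in the IHT mean: − m × D × (1 − r) / (2/3 + m).
- Bias (IHT minus CAU) = IHT shift − CAU shift.

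Low end, f = 0.05 and D = 10: r = 0.0333, m = 0.0111. CAU shift +0.33. IHT shift −0.0111 × 10 × 0.9667 / 0.6778 = −0.16. Bias −0.49 days.

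High end, f = 0.20 and D = 40: r = 0.1333, m = 0.0444. CAU shift +5.33. IHT shift −0.0444 × 40 × 0.8667 / 0.7111 = −2.17. Bias −7.50 days.

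| f | D = 10 | D = 20 | D = 40 | IHT share |
|---|---|---|---|---|
| 5% | −0.49 | −0.98 | −1.97 | 0.678 |
| 10% | −0.97 | −1.94 | −3.87 | 0.689 |
| 20% | −1.88 | −3.75 | −7.50 | 0.711 |

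Negative values favour IHT. The range is 0.49/20 = 2.5% to 7.5/20 = 37.5% of the planned effect. The IHT share moves only from 0.667 to at most 0.711, so the achieved ratio would be a weak alarm.

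**The case against.** The case for the design is considerable.

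- **Re-entering the same data cannot change the arm.** Preventing that is the purpose of the seed. A reader might infer that staff can change the arm simply by running the tool again. The text does not support this: a seed field would have to differ, and the article does not name the seed fields. They may be stable identifiers, possibly combined with a secret element.
- **Eligibility comes before allocation in the text, and a psychiatrist makes the admission judgement.** A reader might infer that allocation is not concealed at all, or that the IHT staff who see the arm are the ones who decide eligibility. Neither is stated. Placement desks also run the tool, and learning the arm afterwards is normal in an open-label trial.
- **Each result goes to the research team,** which could expose conflicting duplicates.
- **An article may leave seed fields and duplicate handling to the full protocol.**
- **Simple randomisation is valid.** A reader might count the lack of balance within organisation as part of the defect. It is not: independent draws cause no bias, and organisation is already a random factor in the model (Statistical analysis).

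These points stand, and they limit the conclusion to what is not assured. They do not remove it. Making the arm depend on entered characteristics is a stated choice, not an omitted detail, and it protects only against identical repeats. Notifying the research team allows detection but does not prevent a second draw, and no rule says which result counts.

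**Conclusion.** The point holds in this limited form. The stated method makes the arm a deterministic function of entered patient characteristics, in a tool run by staff who see the result and some of whom deliver IHT. One arm per patient is guaranteed only when the seed entries agree, and concealment is not assured as described. The documents do not show that any arm has been changed, that staff can predict it, or that concealment has failed.

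The size of any bias is unknown. The range of about 0.5 to 7.5 days rests wholly on assumed rates and severity differences, on movement in one direction only, and on an altered entry acting as an independent draw. It shows that modest discordance could matter against a 20-day target; it is not an estimate. The case for change is that a simple alternative meets the trial's own aim of one arm per patient better than the seed does.

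**What to change.** Change the tool so that it works in this order:

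1. Register the patient and lock the eligibility entries before any arm is shown.
2. Draw the arm centrally, 2:1, independently of the entered characteristics, and store it.
3. On any repeat entry, return the stored arm. Match on more than one identifier, since a single mistyped identifier would register the patient as new.
4. If entries for one patient disagree, let the first allocation stand.
5. Log every repeat or edited entry.
6. Report all pre-randomised patients by arm. The analysed set stays limited to consenting patients, as Design and Consent and mental competence require.

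Stratified blocking by organisation could be added at the same time, but it is optional.

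The cost is a small change to the online tool and an amendment submitted to the ethics committee (Monitoring, quality assurance and approvals). Allocations already made stand, and the sample size is unaffected.

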All patients who meet the inclusion criteria, none of the exclusion criteria, and who are mentally competent to give an informed consent will be approached by the research team and receive information about the study. The patient and his relatives will receive an information folder describing the CAU and IHT interventions and study procedures. An appointment will be made to inform the patient about treatment allocation, answer any questions the patient may have regarding the study and to collect the written informed consent if possible. Consent will be sought regarding (1) the treatment condition they are allocated to, (2) the baseline and follow-up measurements, (3) to inform their relatives, (4) informing their general practitioners, other mental health professionals, (5) informing and asking their pharmacist about drug use, (6) to request and use their data from Statistics Netherlands (Centraal Bureau voor de Statistiek (CBS)). A patient can also participate in this study by giving informed consent to using existing data sources such as their Electronic Health Record (EHR) and CBS data only – EHR data is sufficient to test our primary hypothesis (number of hospitalisation days).

If the patient hesitates about providing informed consent, (s)he will have 5 more days to decide to participate. Only after providing written informed consent, baseline measurements are administrated. If a patient decides not to provide informed consent, (s)he is not included in the study (and can receive any treatment deemed necessary).

